# 3.0 Methods

This randomized-controlled feasibility trial will recruit patients over 19-months from 2 centers (Hamilton ON and London ON).

## 3.1 Study population, inclusion and exclusion criteria

All 17- and 18-year-olds with a pediatric-onset rheumatic disease attending their last pediatric rheumatology appointment prior to transferring to adult care will be assessed for eligibility by the pediatric rheumatologist (Drs. [name], [name], and [name] at McMaster, [name] at Western). Participants will be eligible if they are able to communicate in English, have access a device capable of videoconference or a phone and are available over the subsequent 8-months. Those with a cognitive impairment preventing participation in the individualized education sessions as determined by the medical staff will be excluded. As a feasibility trial, we will document the number of patients who are ineligible and the reason for ineligibility to address this in the future study.

## 3.2 Recruitment

Pediatric rheumatologists will identify patients attending their scheduled last pediatric rheumatology appointment before transferring to adult care. The pediatric rheumatologist will inform the patient about the study and document reasons for ineligibility, as applicable. Interested patients will be directed to the a research assistant who will provide further information and obtain consent.

## 3.3 Sample size

Our sample size is based on the more conservative of our two primary feasibility outcomes: ≥90% of TCI sessions attended. Assuming this, we will require a sample size of 97 for estimating the expected proportion with 6% absolute precision and 90% confidence ^21^. With an average of 7 patients transferring from pediatric to adult care each month (5 Hamilton, 2 London), we will approach 133 patients over 19 months. With an 85% consent rate ^22^ and a 90% study completion rate (133 x 85% x 90% = 102), we will ensure that we meet our sample target of 97 participants completing the study.

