## 3.4 Randomization

Consenting participants will be randomly allocated to the Transition Coach Intervention (TCI) or the control group using the Robust Randomization App ^23^ to generate a site-stratified computer-generated block randomization list with random varying permutated blocks of 4 and 6 and a 1:1 allocation ratio.

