## 3.5 Intervention

All participants (TCI and control group) will receive a paper and electronic copy of the Youth Transition Roadmap (YTR) ^24^, which informs youth about differences between adult and pediatric care and discusses 5 domains of healthcare transition; Self-Advocacy, Medication Management, General Health, Lifestyle Issues and Future Planning related to education and vocation.

All participants will be scheduled for their first adult rheumatology visit (Drs. [name], [name], [name]) within 3-months of consent. The timing of subsequent clinical visits will be at the adult rheumatologist’s discretion. All participants will receive standard of care from their rheumatologists.

Contact information for participants allocated to the TCI group will be provided to the Transition Coaches (TCs) who will schedule participants for their first TC session within 1 month of consent. Sessions with the TCs will be virtual (by videoconference or phone, at the participant’s preference) and will be independent of clinical visits with the adult rheumatologists. There will be 8 monthly sessions, 6 with as ACPAC physiotherapist and 2 with a social worker. The topics will be as follows:

ACPAS physiotherapist transition coach sessions:

- Pediatric to adult care
- Self-advocacy
- Medication management
- General health
- Lifestyle and behaviours
- Future planning

SW transition coach sessions:

- Screening for anxiety and depression (PHQ4)
- Depending on the participant’s self-identified areas of need, topics including:
  - Disease severity, daily impact, current treatment and possible side effects
  - Biologic life transitions
  - Self-management skills
  - Pain management and coping strategies
  - Body image, confidence
  - Living situation, parental/sibling support
  - Ability to partake in social/recreational activities
  - Social relationships/networks
  - Sleep/motivation/energy
  - Anxiety, depression, anger, denial (grief, feelings associated with loss)
  - Lack of validation from others
  - Communicating effectively with medical team/self-advocacy
  - Coping/accommodations with school
  - Being different than others
  - Becoming aware of negative thought patterns and education surrounding learning to recognize depressive thought patterns and strategies
  - Uncertainty/fear about the future

Neither TC will have any contact with the control group for the duration of the study to minimize potential for cross contamination.

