# 5.0 Statistical Analysis

We will use frequencies (numbers and proportions) to report all feasibility outcomes related to Aim 1 including satisfaction questionnaires. Open-ended responses from participants and TCs will be used to inform modifications and refinement of the TCI for the fully powered study.

For Aim 2, descriptive statistics will summarize demographic characteristics and clinical outcomes at each time point. Baseline descriptors will also be summarized by sex and gender.

We will examine within-person, within-group and between-group changes in each PROMIS® outcome and will perform sub-analyses by sex and gender. We will determine means, medians, standard deviations and interquartile ranges as appropriate, at baseline and both follow-up times and calculate variability in changes over time. We will not perform statistical analyses of these changes or group differences as we are underpowered to detect them but will use these to calculate a sample size for a future fully powered study.

Data will be analysed using SPSS v.26 (IBM, New York, United States). Data analyses will be supervised by Drs. [name] and [name] who will support trainees in developing data analysis skills.

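### The 97 in Section 3.3 is sized for coaching-session attendance but filled from both arms; the TCI arm alone gives about ±6.5 to ±7.1 points at 90% confidence, not ±6

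*Protocol*

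**What the plan says.** Section 3.3 names the outcome that drives the sample size: "Our sample size is based on the more conservative of our two primary feasibility outcomes: ≥90% of TCI sessions attended". It continues: "we will require a sample size of 97 for estimating the expected proportion with 6% absolute precision and 90% confidence". To reach that number, "we will approach 133 patients over 19 months", and the section applies an 85% consent rate and "a 90% study completion rate (133 x 85% x 90% = 102"). It concludes that "we will ensure that we meet our sample target of 97 participants completing the study". The 133 are all patients approached at both sites, before randomisation.

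Section 3.4 sets "a 1:1 allocation ratio". Section 3.5 gives eight monthly sessions to the TCI group and adds: "Neither TC will have any contact with the control group for the duration of the study". The footnote to the assessment schedule in Section 4.0 also limits the sessions to the intervention group.

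Section 2.0 sets the attendance criterion at 90% or more of virtual sessions. On reporting, Section 5.0 says: "We will use frequencies (numbers and proportions) to report all feasibility outcomes related to Aim 1".

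**The concern.** The calculation asks how many participants are needed to estimate attendance. The answer is then used as the size of the whole trial, although half the trial has no sessions to attend. Nothing in the protocol doubles the 97 for the control arm, says that 97 are needed in the TCI arm, or describes a calculation based on sessions.

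Attendance is one of five feasibility criteria and the only one for which Section 3.3 states a precision. The results are meant to inform a multicentre trial, so a reader of the protocol would credit the attendance estimate with more certainty than its stated basis supports.

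**Working it through.** **Inputs.** Expected attendance p = 0.90, half-width d = 0.06, 90% confidence (taken as two-sided) and n = 97, all from Section 3.3. Allocation 1:1 from Section 3.4. Eight sessions per TCI participant from Section 3.5.

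**Step 1: the plan's own figure.** n = z² p(1−p)/d², where p(1−p)/d² = 0.09/0.0036 = 25.
- 90% confidence: 1.645² × 25 = 67.6, so 68.
- 95% confidence: 1.960² × 25 = 96.04, so 97.

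The 97 is reproduced at 95%, not at the stated 90%. Other interval methods at 90% do not give 97 either: Wilson gives 70, and the continuity-corrected and Clopper-Pearson methods each give 84. Using the 85% consent target for p at 90% confidence gives 96, which is close, but that is not the outcome the section names.

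**Step 2: how many participants have sessions.**
- Half of 97 completers: 48 or 49.
- Half of 133 × 0.85 × 0.90 = 101.7, about 102 completers: 51.
- Half of 133 × 0.85 = 113 randomised: about 57.

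**Step 3: precision with the participant as unit.** Half-width = z √(0.09/n).

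| n | Who | 90% confidence | 95% confidence |
|---|---|---|---|
| 97 | both arms, as the plan counts | ±5.0 | ±6.0 |
| 49 | TCI, half of 97 completers | ±7.1 | ±8.4 |
| 51 | TCI, half of 102 completers | ±6.9 | ±8.2 |
| 57 | all randomised to TCI | ±6.5 | ±7.8 |

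Worked example for n = 49 at 90%: 1.645 × √(0.09/49) = 1.645 × 0.0429 = 0.0705. The ±6 is missed in every TCI row at both confidence levels.

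**Step 4: precision with the session as unit.** With m participants, eight sessions each and within-person correlation ICC, the half-width is z √(0.09 (1 + 7·ICC)/(8m)). Setting this to 0.06 gives the largest ICC at which ±6 still holds: ICC = [8m × 0.0036/(z² × 0.09) − 1]/7.

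| m | Largest ICC, 90% | Largest ICC, 95% |
|---|---|---|
| 49 | 0.69 | 0.44 |
| 51 | 0.72 | 0.46 |
| 57 | 0.82 | 0.54 |

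For m = 57 at 90%: 8 × 57 × 0.0036 = 1.6416; 1.6416/0.2435 = 6.74; (6.74 − 1)/7 = 0.82. The protocol gives no ICC, so the result is a range. With m = 49 the half-width at 90% runs from ±2.5 (ICC 0) to ±7.1 (ICC 1).

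**The case against.** The strongest reply is that both statements of the criterion, in Sections 2.0 and 3.3, speak of sessions, not of people. On that unit the TCI arm supplies 392 sessions (49 × 8) or more, and ±6 at the stated 90% confidence survives quite strong within-person correlation. This stands in part. A reader might infer that the trial cannot estimate attendance to within 6 points at all; the documents do not support that. What they support is that the justification is wrong: Section 3.3 applies a single-proportion calculation, counts participants, gives no ICC and describes no session-level analysis.

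A reader might also infer that attendance will be analysed in completers only, which would tend to raise it, because Section 3.3 frames its target on completers. That phrase closes a recruitment calculation, and no section plans such an analysis. Nor does Section 5.0 plan a simple binomial interval over pooled sessions; it plans numbers and proportions. The attendance denominator and any variance method may be set out in an analysis plan that is not at hand, so their absence here is not an error.

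Finally, Section 2.0 sets thresholds without tying them to a confidence interval. The misstated precision therefore does not by itself change whether the criterion is met. This limits the consequence but does not make the stated precision correct.

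**Conclusion.** The point holds as a fault in the stated sample-size basis. The 97 comes from an outcome that only about half of those participants can contribute to. On the participant unit that the calculation implies, and at 90% attendance, the shortfall against ±6 at the stated 90% confidence is about half a point to just over one point, depending on whether all 57 randomised to TCI or 49 completers are counted. At 95%, the level that actually yields 97, it is about 1.8 to 2.4 points.

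These figures assume equal arms, the section's own consent and completion rates, and a normal-approximation interval. On the session unit, whether ±6 is met is unknown without an ICC.

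The mismatch between 97 and the stated confidence level is a separate error. It does not rescue the plan: the TCI arm falls short of 68 as well as of 97.

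**What to change.** In Section 3.3:
- Restate the attendance precision for the TCI arm, with its n: about 57 randomised, about 49 to 51 completers. Say which count is used and whether the unit is the participant or the session. If it is the session, state the assumed ICC or a range.
- Correct the confidence level so that it matches the calculation.
- Keep 97 as the total only for outcomes to which both arms contribute, such as 8-month completion and missing data.

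Optionally, state that attendance is counted over all participants randomised to TCI, and that any interval reported allows for clustering by participant.

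The cost is wording and a less favourable stated precision; no extra patients are needed. Holding ±6 in the TCI arm with the participant as unit would cost far more:
- **90% confidence:** 2 × 68 = 136 completers, or 136/(0.85 × 0.90) = about 178 approached, about 25 months at 7 a month.
- **95% confidence:** 2 × 97 = 194 completers, about 254 approached, about 36 months.

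Restating the precision is the proportionate choice for a feasibility trial.

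### The accrual forecast in Protocol 3.3 has no eligibility step, so 102 completers is a best-case expectation and does not guarantee 97

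*Protocol*

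**What the plan says.** Section 3.3 (Sample size) builds the forecast in four steps.

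- Source: "With an average of 7 patients transferring from pediatric to adult care each month (5 Hamilton, 2 London").
- Number approached: "we will approach 133 patients over 19 months".
- Losses: "With an 85% consent rate" and "a 90% study completion rate (133 x 85% x 90% = 102").
- Conclusion: "we will ensure that we meet our sample target of 97 participants completing the study".

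The target comes from the same paragraph: "we will require a sample size of 97 for estimating the expected proportion with 6% absolute precision and 90% confidence".

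Section 3.1 applies entry criteria to the patients who make up the 133. It begins "Participants will be eligible if they are able to communicate in English, have access a device capable of videoconference or a phone", adds availability over the following 8 months, and excludes cognitive impairment that prevents participation. It then says "we will document the number of patients who are ineligible and the reason for ineligibility". Section 3.2 also has the pediatric rheumatologist record reasons for ineligibility.

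**The concern.** The 133 equals the full transfer volume, 7 x 19. For the forecast to hold, every transferring patient must be eligible and approached. Sections 3.1 and 3.2 do not assume this; they set up a screen and a log of those who fail it. The product in 3.3 thus omits a loss that the protocol itself expects. It also presents a mean as a guarantee.

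Feasibility is the primary objective, and recruitment is among the data for the primary outcome (section 4.0). If the forecast leaves out eligibility, observed accrual will be judged against too favourable a yardstick, and the same omission may carry over into planning the multicentre trial.

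**Working it through.** **Inputs.** From 3.3: 7 transfers a month, 19 months, 85% consent, 90% completion, target 97, and an expected proportion of 90% with 6% precision at 90% confidence. From 3.4: 1:1 allocation. The ineligible share *i* is not given anywhere, so 0 to 15% is an assumed range.

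**Reproducing the plan's figure.** 7 x 19 = 133. 133 x 0.85 x 0.90 = 101.7, printed as 102. The multiplication is correct.

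**Break-even.** Eligible patients needed for an expected 97 completers: 97 / (0.85 x 0.90) = 97 / 0.765 = 126.8. Margin: 133 - 126.8 = 6.2 patients, and 6.2 / 133 = 4.7%.

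**Expected completers and chance of at least 97.** The expected count is 133 x (1 - *i*) x 0.765. With 133 transfers fixed, completers are Binomial(133, 0.765 x (1 - *i*)). Section 3.3 calls 7 a month an average, so the alternative lets transfers vary as Poisson with mean 133; completers are then Poisson with the expected count as mean.

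| Ineligible (assumed) | Expected completers | P(at least 97), 133 fixed | P(at least 97), Poisson |
|---|---|---|---|
| 0% | 101.7 | 0.86 | 0.69 |
| 5% | 96.7 | 0.52 | 0.50 |
| 10% | 91.6 | 0.18 | 0.30 |
| 15% | 86.5 | 0.03 | 0.14 |

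The first row needs no assumption about ineligibility: with every planning rate exactly right, 97 is likely but not assured.

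**Other inputs.** With nobody ineligible, the expected count also falls below 97 if consent is under 97 / (133 x 0.90) = 81.0%, or completion under 97 / (133 x 0.85) = 85.8%.

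**What a shortfall costs.** The required number is n = z² x 0.90 x 0.10 / 0.06².

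- At 90% confidence (z = 1.645) this is 67.6, so 68.
- At 95% confidence (z = 1.96) it is 96.04, so 97.

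The printed 97 therefore matches 95% confidence, not the stated 90%. Against 68, the expected count stays sufficient until 1 - 68 / 101.7 = 33% are ineligible. At 15% ineligible the chance of at least 68 completers is above 0.99 (133 fixed) or 0.98 (Poisson).

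**Precision for the sizing outcome.** Section 3.3 sizes the trial on attendance at TCI sessions, and only the TCI arm has sessions. Half of 86.5 to 101.7 is about 43 to 51 completers. Treating each as one observation, the half-width is z x sqrt(0.09 / n):

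- 90% confidence: 1.645 x sqrt(0.09 / 51) = 6.9 points, to 1.645 x sqrt(0.09 / 43) = 7.5 points.
- 95% confidence: 1.96 x sqrt(0.09 / 51) = 8.2 points, to 1.96 x sqrt(0.09 / 43) = 9.0 points.

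**The case against.** The strongest reply is that little follows from this. Over all completers the stated 6% at 90% confidence needs 68, which is reached comfortably across the assumed range. Even if 95% was intended, 87 completers give 1.96 x sqrt(0.09 / 87) = 6.3 points against 6.0 with 97, in a feasibility trial that plans no statistical tests of group differences. This stands, and it limits the weight of the point.

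A second reply is that the ineligibility rate is unknown, the criteria are permissive (a phone suffices), and 3.1 openly treats ineligibility as something to be measured for the future study. This also stands: nothing in the protocol shows that 5, 10 or 15% is realistic. It does not justify an implicit zero, nor a guarantee.

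A third reply is that the 7 a month might already be net of ineligible patients, or that the 85% might be taken over everyone transferring. The text describes the 7 as patients transferring and the 85% as a consent rate, so neither reading is the natural one. On either reading the chance of 97 would still be 0.86 or 0.69.

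A reader might infer three stronger conclusions that the documents do not support:

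- That the target is lost at 5% ineligible. At 5% the odds of reaching 97 are about even.
- That 3.3 contains a multiplication error in the accrual product. It does not; the gap is a missing factor and an overstated conclusion.
- That the trial must enrol more patients or cannot answer its feasibility questions. The precision figures above do not show that.

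**Conclusion.** The point holds in a limited form. Section 3.3 treats all 133 transferring patients as eligible and approached, although 3.1 and 3.2 expect some not to be. The 102 is a best-case mean, with a margin of 4.7% of those approached, and the guarantee of 97 has no support: the chance is 0.86 or 0.69 even with no ineligible patients, and roughly even at 5%.

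The probabilities rest on the protocol's consent and completion rates being exactly right, on independent patients, and on fixed or Poisson transfers. The ineligible shares are assumptions. The defect is an unsupported forecast and guarantee, not a loss of the trial's conclusions. It should be corrected because the correction is nearly free and accrual is part of what the trial is meant to assess.

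**What to change.** In section 3.3:

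1. Write the forecast as 133 x eligible share x 85% x 90%, and state the assumed eligible share and its basis.
2. Replace the guarantee with the expected number and a range, for example 86.5 to 101.7 completers (roughly 87 to 102) for 85% to 100% eligible.
3. If precision for session attendance is restated, base it on the TCI-arm completers (about 43 to 51), not on all completers. A figure over all completers would overstate the precision of the outcome that sizes the trial.

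The cost is a few lines of text and a slightly less favourable stated forecast. No extra enrolment is needed.

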## 3.4 Randomization

Consenting participants will be randomly allocated to the Transition Coach Intervention (TCI) or the control group using the Robust Randomization App ^23^ to generate a site-stratified computer-generated block randomization list with random varying permutated blocks of 4 and 6 and a 1:1 allocation ratio.

## 3.5 Intervention

All participants (TCI and control group) will receive a paper and electronic copy of the Youth Transition Roadmap (YTR) ^24^, which informs youth about differences between adult and pediatric care and discusses 5 domains of healthcare transition; Self-Advocacy, Medication Management, General Health, Lifestyle Issues and Future Planning related to education and vocation.

All participants will be scheduled for their first adult rheumatology visit (Drs. [name], [name], [name]) within 3-months of consent. The timing of subsequent clinical visits will be at the adult rheumatologist’s discretion. All participants will receive standard of care from their rheumatologists.

Contact information for participants allocated to the TCI group will be provided to the Transition Coaches (TCs) who will schedule participants for their first TC session within 1 month of consent. Sessions with the TCs will be virtual (by videoconference or phone, at the participant’s preference) and will be independent of clinical visits with the adult rheumatologists. There will be 8 monthly sessions, 6 with as ACPAC physiotherapist and 2 with a social worker. The topics will be as follows:

ACPAS physiotherapist transition coach sessions:

- Pediatric to adult care
- Self-advocacy
- Medication management
- General health
- Lifestyle and behaviours
- Future planning

SW transition coach sessions:

- Screening for anxiety and depression (PHQ4)
- Depending on the participant’s self-identified areas of need, topics including:
  - Disease severity, daily impact, current treatment and possible side effects
  - Biologic life transitions
  - Self-management skills
  - Pain management and coping strategies
  - Body image, confidence
  - Living situation, parental/sibling support
  - Ability to partake in social/recreational activities
  - Social relationships/networks
  - Sleep/motivation/energy
  - Anxiety, depression, anger, denial (grief, feelings associated with loss)
  - Lack of validation from others
  - Communicating effectively with medical team/self-advocacy
  - Coping/accommodations with school
  - Being different than others
  - Becoming aware of negative thought patterns and education surrounding learning to recognize depressive thought patterns and strategies
  - Uncertainty/fear about the future

Neither TC will have any contact with the control group for the duration of the study to minimize potential for cross contamination.

If any concerns be identified in the coaching sessions or on the screening questionnaires, the transition coach will inquire about current treatments and supports. Should further follow up/support be required, the transition coach will contact the patient's family doctor via their rheumatologist. The social worker transition coach may also connect with [name] (adolescent medicine specialist) for further support if required.

Questionnaires evaluating global function, self-efficacy and transition readiness will be administered at baseline, 8 months and 11 months.

